### Recruitment

Adolescents with a depressive disorder referred for treatment in psychiatric care and their parents will be informed about the study and asked to participate. Researchers will obtain written informed consent from adolescents, and parents when adolescents are younger than 16 years, before enrolling participants in this study. Additional written informed consent will be obtained from parents when they participate in the study. All adolescents meeting the eligibility criteria and willing to participate will be assigned to the D(o)epression Blended intervention.

### Sample Size

The sample size (N=70) is equal to the sample size of the RCT that was already conducted in which D(o)epression face-to-face was compared with TAU. The data from this study will be compared with data from that RCT. The power analysis used in the previously conducted RCT was based on the difference between CBT and TAU at posttreatment. A meta-analysis on the effectiveness of CBT showed an effect size of 0.53 for CBT when delivered face-to-face [7]. Based on a meta-analysis on online interventions for depression (among which preventive interventions), the effect size was 0.76 [14]. Based on the literature, we assume that the effect size of blended CBT is equal to face-to-face CBT. We hypothesize that D(o)epression Blended is more effective than TAU. Furthermore, we will exploratively compare D(o)epression Blended to D(o)epression face-to-face. To detect the difference in depression diagnoses between the conditions of the previous study comparing blended CBT with TAU and this study, assuming alpha=.05 with a power of (1-β)=0.80 and dropout of 20% (power calculations in Stata), 70 adolescents will be included in this study.

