**Methods:**

A pragmatic quasi-experimental controlled trial will be conducted to study the effectiveness of a blended CBT treatment protocol, in which blended CBT is compared with face-to-face CBT (n=44) and treatment as usual (n=44); the latter two were collected in a previous randomized controlled trial. The same inclusion and exclusion criteria will be used: adolescents aged between 12 and 21 years, with a clinical diagnosis of a depressive disorder, and referred to one of the participating mental health institutions. Assessments will be conducted at the same time points: before the start of the intervention, during the intervention (after 5 and 10 weeks), postintervention, and at 6- and 12-month follow-ups.

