## Results

### Overview

The primary outcome is the presence of a depression diagnosis at 12-month follow-up. Several secondary outcomes will be measured, such as depressive symptoms, quality of life, and suicide risk. Costs and effects in both conditions will be compared to analyze cost-effectiveness. Further, moderating (age, gender, alcohol and drug use, parental depression, and other psychopathology) and mediating (negative automatic thoughts, cognitive emotion regulation, attributional style) effects will be tested. Also, treatment characteristics will be studied, such as characteristics of the therapists, treatment expectancy, and therapeutic alliance. The dropout rate and treatment characteristics will be measured to study the feasibility of blended CBT.

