### Recruitment

The trial began recruiting participants in November 2017, and end of study enrollment was March 2019. At this time, 42 children have been recruited.

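### The 80% power claim for 70 patients does not fit comparators fixed at 44 each or the 42 patients enrolled, and 70 matches no stated size of the earlier trial

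*Protocol article*

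**What the plan says.** The Sample Size section justifies the new cohort in two ways. First, it equates it with the earlier trial: "The sample size (N=70) is equal to the sample size of the RCT that was already conducted". Second, it gives a power statement for diagnoses, blended CBT against TAU: "assuming alpha=.05 with a power of (1-β)=0.80 and dropout of 20% (power calculations in Stata), 70 adolescents will be included in this study". The only effect sizes in the section are 0.53 (face-to-face CBT) and 0.76 (online interventions), and blended CBT is assumed to match face-to-face CBT. No diagnosis percentages are given. The section adds that the earlier trial's own power analysis was "based on the difference between CBT and TAU at posttreatment".

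Three other places bear on this:

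- Abstract, Methods: "blended CBT is compared with face-to-face CBT (n=44) and treatment as usual (n=44"). Both comparator groups come from the completed trial.
- Results, Overview: "The primary outcome is the presence of a depression diagnosis at 12-month follow-up". Analysis of Primary Outcome treats it as dichotomous, tested by logistic regression.
- Results, Recruitment: "end of study enrollment was March 2019. At this time, 42 children have been recruited". Trial Status describes only follow-up assessments as still in progress.

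The power statement is not qualified for any of these, and Strengths and Limitations does not mention power.

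**The concern.** The stated equality fails on the article's own figures, because 70 is neither 44 nor 88. The power claim is also hard to square with the sizes. An 80% figure that needs about equal arms cannot simply carry over to a comparator already fixed at 44, and still less once 42 rather than 70 patients have been enrolled.

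This affects how a null result is read. The stated hypothesis is that blended CBT is superior to TAU. The Introduction reports that face-to-face CBT did no better than TAU in the earlier trial, and the Sample Size section assumes blended CBT is like face-to-face CBT, so a non-significant primary result is quite possible. A reader who trusts 80% power could take that result as evidence of no benefit when the study could not have settled the question.

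**Working it through.** **Inputs.** From Sample Size: alpha 0.05 (taken as two-sided; not stated), power 0.80, dropout 20%, effect sizes 0.53 and 0.76. From the Abstract: TAU 44. From Recruitment: 42 blended patients.

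**1. Reproducing 70.** For two equal groups, n per arm = 2(1.960 + 0.842)²/d².

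- d = 0.53: n = 55.9, so 56 per arm, and 56/0.80 = 70 in **each** arm. A t-based calculation gives 57, and 57/0.80 = 71.25, so 72.
- d = 0.76: n = 27.2, so 28 per arm, and 28/0.80 = 35 per arm, or 70 over **two** arms.

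Both give 70. The first fits better, because the section assumes the face-to-face effect for blended CBT and puts all 70 in the single new cohort. The formula is not printed, so this remains an inference.

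**2. Power at d = 0.53 with the actual sizes.** Two-sided t-test, noncentrality d√(n₁n₂/(n₁+n₂)). With 20% loss, 70 becomes 56, 42 becomes 34 (33.6) and 44 becomes 35 (35.2).

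| Blended v TAU | Meaning | Noncentrality | Power |
|---|---|---|---|
| 56 v 56 | equal arms, the inferred design | 2.80 | 79% |
| 70 v 44 | planned cohort, no loss | 2.76 | 78% |
| 56 v 44 | planned cohort, loss in blended arm only | 2.63 | 74% |
| 42 v 44 | enrolled, no loss | 2.46 | 68% |
| 34 v 44 | enrolled, loss in blended arm only | 2.32 | 63% |
| 34 v 35 | enrolled, loss in both arms (assumption) | 2.20 | 58% |

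The fixed comparator alone costs little. The shortfall grows with dropout and with the reduced enrolment.

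**3. The binary primary outcome.** The article gives no diagnosis rates, so two assumptions are needed. The first is the logistic conversion, OR = exp(0.53 × π/√3) = 2.62. The second is a range of 15% to 80% for the TAU diagnosis rate at 12 months. Power is for the usual two-proportion test.

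Example with TAU at 50%: the blended odds are 1/2.62 = 0.382, a rate of 27.7%. At 42 v 44 the pooled rate is 0.391, the null standard error 0.105 and the alternative standard error 0.102. Then (0.223 − 1.96 × 0.105)/0.102 = 0.167, which gives 57% power.

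| TAU rate | Blended rate | 42 v 44 | 34 v 44 | 34 v 35 |
|---|---|---|---|---|
| 15% | 6.3% | 25% | 21% | 21% |
| 30% | 14.1% | 43% | 37% | 35% |
| 50% | 27.7% | 57% | 51% | 48% |
| 60% | 36.5% | 59% | 54% | 50% |
| 80% | 60.5% | 51% | 47% | 43% |

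Even 56 v 56 reaches at most 71% under this conversion.

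**4. What the study can detect or estimate.** The difference detectable with 80% power is as follows.

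- 42 v 44: 29 points from a TAU rate of 50% (to 21%), or 23 points from 30% (to 7%).
- 34 v 35: 32 and 25 points respectively.

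For 27.7% v 50% at 42 v 44, the 95% CI half-width is 1.96√(0.25/44 + 0.200/42) = 0.20, about ±20 percentage points.

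**The case against.** The strongest case against is that the design calculation is not shown. The section says it concerned diagnoses, so it may have been binary from the start, with the 44 already allowed for. For illustration, 50% v 23% at 56 v 44 gives (0.27 − 1.96 × 0.0960)/0.0941 = 0.87, or 81% power. That cannot be excluded. It does not rescue the claim at the enrolled size: the same rates give (0.27 − 1.96 × 0.1040)/0.0995 = 0.66, or 75%, at 42 v 44, and (0.27 − 1.96 × 0.1110)/0.1044 = 0.50, or 69%, at 34 v 44.

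Four stronger readings are tempting and are not supported:

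- **That 70 can only be a per-arm figure from 0.53.** The 0.76 route also yields 70, over two arms. At 0.76, 42 v 44 would have about 94% power, but the section does not assume 0.76 for blended CBT.
- **That this trial was powered at posttreatment.** That time point is stated for the earlier trial's analysis. None is given for this one.
- **That TAU must lose a further 20%.** Those data are already collected, and the article does not say whether 44 means randomised or assessed at 12 months. Imputed intention-to-treat analysis is also planned. The 34 v 35 figures are therefore an assumption.
- **That the trial is more likely than not to miss its effect.** At 0.53 every scenario above exceeds half. Power falls below half only on the assumed binary conversion, and not at every TAU rate.

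It is also fair that enrolling 42 is a matter of conduct, openly reported, that 70 may have been the earlier trial's planned size (not shown), and that the Discussion calls the evidence preliminary. None of this reconciles 70 with 44 and 44, supplies the missing rates, or qualifies the 80%.

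**Conclusion.** The point holds in this form. The equality with the earlier trial contradicts the article's own 44 and 44. The 80% claim names diagnoses but rests on no stated diagnosis rates, and it stands unqualified beside a fixed TAU arm of 44 and 42 enrolled patients.

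On the likeliest reconstruction (0.53, two-sided), the shortfall is small for 70 v 44 without loss (78%). It is clear for 42 v 44 (68%) and larger after 20% loss (63% if only the blended arm loses patients, 58% if both do). On the 12-month binary outcome, power is about 25% to 59% at 42 v 44 and 21% to 54% after loss. Those ranges depend on the conversion to an odds ratio of about 2.6 and on the assumed TAU rates of 15% to 80%.

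That 42 is the final number depends on reading the recruitment count together with the March 2019 end of enrolment in the same section.

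**What to change.** Revise the Sample Size wording:

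1. Remove the statement that 70 equals the earlier trial's sample size, or reconcile it with 44 per arm and 88 in total.
2. Keep 80% only as the a priori planning target, give the diagnosis rates it assumed, and state that the design does not deliver it.
3. State that the comparators are fixed at 44 and 44 and that 42 were enrolled in the blended arm.
4. Give the detectable difference or the expected 95% CI width for the 12-month diagnosis percentage, at 42 v 44 and after 20% loss, over a stated range of TAU rates. Say which arms the loss applies to.
5. State that a non-significant primary result will be reported as inconclusive, with its 95% CI.

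No further enrolment or data collection is needed. The cost is that a stated figure becomes less favourable.

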## Introduction

Depressive disorders are among the most prevalent mental health disorders in adolescents [1]. They have a substantial effect on well-being, a high burden of disease, and a high risk of recurrence and chronicity [1,2]. At the age of 18 years, more than 15% of adolescents have suffered from a major depressive disorder [3]. Depression shows high comorbidity with other mental health diagnoses and increased social problems, decreased academic performance, increased school dropouts, more substance abuse, and an increased risk of suicide attempts and suicide [1,2,4]. Therefore, it is crucial that depressive disorders are treated effectively at an early age. In this study, we will test the effectiveness and cost-effectiveness of a blended treatment protocol [5] that combines internet-based and face-to-face sessions in an integrated treatment protocol targeting depressive symptoms in clinically depressed adolescents.

Several meta-analyses have shown that cognitive behavioral therapy (CBT) is an effective intervention to treat adolescent depression [6,7]. However, the effect size of CBT was found to be moderate (Cohen’s *d*=0.53) [7], and 50% of the adolescents were not free of depressive symptoms after being treated [8]. A recent Dutch randomized controlled trial (RCT) showed that the D(o)epression protocol (face-to-face individual CBT) was equally effective as treatment as usual (TAU; for example, interpersonal therapy, family therapy, medication, mindfulness training, creative therapy, and running therapy) in reducing depressive symptoms, as assessed by the Children’s Depression Inventory 2, and depressive disorders, as assessed by the semistructured interview Kiddie Schedule for Affective Disorders and Schizophrenia (K-SADS) [9,10]. Despite this result, a significant number of adolescents were not free of depressive symptoms at posttreatment (24%), the effects were moderate, the dropout was high (57%), and it was hard to motivate patients to finish the treatment. Therefore, it is important to develop an attractive and more suitable treatment for adolescents who do not prefer to visit a mental health professional each week. Exploring possibilities to improve existing treatments in an innovative manner with recently developed technologies to reach out to patients may prove a fruitful strategy.

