This study will examine the effectiveness and cost-effectiveness of D(o)epression Blended compared with D(o)epression face-to-face and TAU in clinically depressed adolescents. The adolescents in the latter two conditions already participated in a previous study comparing CBT with TAU using an RCT design [9,10]. Blended CBT treatment is expected to be more effective than TAU. Additionally, we expect blended CBT to be equally effective as face-to-face CBT. We also will study the intervention effect of depression severity, quality of life, suicide risk, and comorbidity. The costs of the interventions in the three conditions will be compared to analyze the cost-effectiveness. In addition to examining the effectiveness and cost-effectiveness, we will examine who the intervention is effective for by testing several moderators (age, gender, ethnicity, family income, alcohol and drug use, life events, degree of conflicts, parental depression, and other psychopathology) and how the intervention works by studying several mediators (negative automatic thoughts, cognitive emotion regulation, attributional style). Furthermore, treatment characteristics will be studied; that is, characteristics of the therapists, treatment expectancy, previous treatments, treatment satisfaction, therapeutic alliance, cooperation with treatment, and dropout rates to see whether the feasibility of D(o)epression Blended differs from face-to-face CBT and TAU, and whether these factors are related to the implementation and execution of the treatment program.

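### The 80% power for blended CBT over TAU is not supported by the plan's own premises, which together imply a difference from this TAU arm near zero

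*Protocol article*

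**What the plan says.** The Sample Size section of the protocol article cites two meta-analytic effects. The first is for face-to-face CBT: "A meta-analysis on the effectiveness of CBT showed an effect size of 0.53 for CBT when delivered face-to-face". The second is for online programmes: "Based on a meta-analysis on online interventions for depression (among which preventive interventions), the effect size was 0.76". It then sets the blended effect equal to the face-to-face effect and states superiority over TAU as the hypothesis: "we assume that the effect size of blended CBT is equal to face-to-face CBT. We hypothesize that D(o)epression Blended is more effective than TAU". The comparison with face-to-face CBT is called exploratory. The size of the new cohort is justified by "assuming alpha=.05 with a power of (1-β)=0.80 and dropout of 20% (power calculations in Stata"), giving 70.

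The Introduction repeats both expectations: blended CBT on a par with face-to-face CBT, and "Blended CBT treatment is expected to be more effective than TAU". It also reports the result of the earlier Dutch RCT, in which the D(o)epression protocol ("face-to-face individual CBT) was equally effective as treatment as usual"). That result covers symptoms on the Children's Depression Inventory 2 and depressive disorders on the K-SADS, the instrument of the primary outcome here.

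The Abstract, the Introduction and the Design section make clear that the face-to-face and TAU arms of that RCT (44 patients each, per the Abstract) are the comparators in this study.

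**The concern.** The TAU comparator is not a future group about which little is known. It is a fixed set of patients against whom a treatment with the same content has already been compared, and no difference was reported. If blended CBT is assumed to do as well as face-to-face CBT, and face-to-face CBT did as well as this TAU arm, the expected blended-TAU difference is small at best. A meta-analytic effect from other trials does not describe the difference from this particular arm.

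This affects the only directional hypothesis in the plan. If the true difference is small, a non-significant result was foreseeable and says little about blended CBT. A significant result would need explaining in a non-randomised comparison with an earlier cohort. It could reflect chance, a difference between cohorts, or a blended effect larger than the face-to-face effect, and the last contradicts the planning assumption. The article links a favourable result to wide implementation, so the reading of this contrast matters.

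**Working it through.** **Inputs from the article.** Alpha 0.05, power 0.80, dropout 20%, effects 0.53 and 0.76, target 70 (Sample Size); 44 TAU patients (Abstract); 42 recruited, with enrolment ended in March 2019 (Recruitment, under Results). Two-sided testing is my assumption, because the article does not state sidedness.

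**Reproducing the stated 70.** For two means with equal arms, n per arm = 2(1.960 + 0.842)²/d².

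- d = 0.53: 2 × 7.849/0.2809 = 55.9, so 56 per arm. Allowing for dropout, 56/0.80 = 70. This is an exact match.
- d = 0.76: 27.2, so 28 per arm, and 28/0.80 = 35. No match.
- d = 0.53, one-sided: 45 per arm, and 45/0.80 = 56.25, so 57. No match.

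Of the effects cited, 0.53 with a two-sided test is the simplest route to 70. This is inferred from the match and from where 0.53 is placed.

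**The implied difference.** Write B, F and T for the outcomes under blended CBT, face-to-face CBT and TAU. Then B − T = (B − F) + (F − T). The Sample Size section sets B − F to about 0. The Introduction reports F − T as about 0. The implied point value of B − T is therefore about 0.

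**How much room the RCT result leaves.** The article gives no estimate or interval for F − T. With an assumed 44 analysed per arm, the 95% half-width on d is 1.96 × √(2/44) = 0.42; with 35 per arm (44 less about 20%) it is 1.96 × √(2/35) = 0.47. An observed estimate near zero would therefore exclude 0.53 while leaving differences of 0.1 to 0.3 open.

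**Power if the true difference is small.** Two-sided t-test; the values of d below 0.53 are assumed, and all 44 TAU patients are taken as evaluable. The 56 is the plan's own evaluable number (70 × 0.8). The 42 is the number reported as recruited, before any dropout.

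| True d | 56 v 44 | 42 v 44 |
|---|---|---|
| 0 | 5% | 5% |
| 0.1 | 8% | 7% |
| 0.2 | 17% | 15% |
| 0.3 | 31% | 28% |
| 0.53 | 74% | 68% |

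The 5% at zero is the two-sided rejection rate; in the hypothesised direction it is 2.5%. For 80% power with equal arms, the same formula needs 175 evaluable per arm at d = 0.3, 393 at 0.2 and 1,570 at 0.1. These are approximations on a continuous scale. The primary analysis is a logistic regression of diagnosis, and the article gives no diagnosis rates from which to compute its power directly.

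**The case against.** Four points can be made for the plan, and each limits the finding.

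- **The use of 0.53 is not stated.** The article also ties 70 to the size of the earlier RCT and describes the calculation as one on diagnoses. This stands. The conclusion does not depend on 0.53, however: any effect large enough to give 80% power at this size sits badly with the reported RCT result.
- **Equal effectiveness in the earlier RCT may mean only a non-significant comparison.** No estimate, interval or time point is attached to it, whereas the primary outcome is diagnosis at 12 months. This stands too. A reader might infer that the true difference is exactly zero, or that the three statements are logically incompatible. The article does not support that, because two loose statements of equality are not identities and a modest difference remains possible.
- **There is a rationale for a blended advantage.** The Introduction reports 57% dropout and poor motivation in the earlier RCT, and argues that blended care may improve motivation and reduce dropout. That is a reason to expect blended CBT to beat TAU, but only by beating face-to-face CBT as well, which the Sample Size section assumes it will not do.
- **An optimistic hypothesis does not invalidate the test, and the limitations are acknowledged.** The type I error is unaffected, and the Strengths and Limitations section concedes possible cohort differences and calls the evidence preliminary. That is correct. The defect lies in the stated power and in how a result would be read. A reader might also infer that the superiority hypothesis should be replaced by estimation. With the comparator results already known, that would itself be a post hoc change to a registered study, and it is not needed.

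**Conclusion.** The finding holds in limited form. The 80% power is not supported by the plan's own premises, because these put the expected difference from this TAU arm near zero and the article does not reconcile them. If the true difference is between 0.1 and 0.3, power at the planned evaluable size is roughly 8% to 31%, and with the 42 recruited roughly 7% to 28%. These figures rest on assumed effects, two-sided testing, a t-test approximation to a binary outcome and no loss from the TAU arm. The statement that a near-zero RCT estimate would exclude 0.53 rests on an assumed 44 analysed per arm. Whether the observed 12-month difference is in fact near zero cannot be settled from the article. This should be fixed, since it changes what the blended-TAU contrast can be said to show.

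**What to change.** In the Sample Size section:

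1. Stop using a meta-analytic effect as the expected difference from this TAU arm.
2. Restate the planning difference and the power from the RCT's observed 12-month face-to-face and TAU diagnosis rates, and name the effect and test that were used to reach 70.
3. Either justify an advantage of blended over face-to-face CBT or drop the assumption that the two are equal.

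In the hypotheses and the analysis of the primary outcome, keep the registered superiority hypothesis and report the blended-TAU contrast with a confidence interval. State in advance that it will be read beside the blended v face-to-face contrast and the randomised face-to-face v TAU contrast before it is attributed to treatment.

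The cost is a change of wording and a recalculation from data that the earlier RCT already holds. The stated power will look less favourable. With enrolment closed, the restatement cannot change the sample size, and it should be dated and disclosed as made after the comparator results were known.

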## Abstract

**Background:**

Cognitive behavioral therapy (CBT) is an effective intervention to treat depressive disorders in youth. However, 50% of adolescents still have depressive symptoms after treatment, and 57% drop out during treatment. Online CBT interventions have proven to be effective in reducing depressive symptoms and seem promising as a treatment for depressed adolescents. However, combining online programs with face-to-face sessions seems necessary to increase their effectiveness and monitor for suicide risk.

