### Analyses

Intention-to-treat (imputed data) analyses and completer-only analyses will be conducted. Results will be reported in accordance with the CONSORT (Consolidated Standards of Reporting Trials) 2010 Statement [49].

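### The stated 80% power needs 70 patients in each arm; with the TAU comparator fixed at 44 and 42 blended patients recruited, power at the plan's own 20% dropout is about 58%

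*Protocol article*

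**What the plan says.** - **Power statement (Sample Size).** The comparison to be powered is blended CBT against TAU on depression diagnosis, "assuming alpha=.05 with a power of (1-β)=0.80", with "dropout of 20% (power calculations in Stata), 70 adolescents will be included in this study". The section gives no diagnosis rates. It cites a meta-analysis that "showed an effect size of 0.53 for CBT when delivered face-to-face" and assumes the same effect for blended CBT. It also says that 70 equals the sample size of the earlier RCT.
- **Comparator sizes (Abstract, Methods).** Face-to-face CBT and TAU have 44 patients each, both from that completed RCT.
- **Recruitment (Results).** Enrolment ended in March 2019, and "At this time, 42 children have been recruited".
- **Dropout elsewhere.** The Abstract says "57% drop out during treatment". The Introduction says of the earlier RCT that "the dropout was high (57%), and it was hard to motivate patients to finish the treatment".
- **Analysis sets (Analyses).** "Intention-to-treat (imputed data) analyses and completer-only analyses will be conducted". The text does not say which of the two carries the primary conclusion.

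**The concern.** The power claim tells a reader what a null result would mean. If the trial had 80% power for the effect it names, a non-significant difference from TAU would be fairly strong evidence against an effect of that size. If the real figure is nearer 60%, it would not be.

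One arm of the comparison could not grow, because its data were already collected, and the other closed well short of 70. A calculation with two arms of 70 therefore describes neither the planned comparison (70 v 44) nor the achieved one (42 v 44).

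The dropout allowance is a second, smaller matter. The 20% carries no definition, and the same article reports 57% dropout for the RCT that supplies both comparators. What that means for the trial depends on whether dropout refers to stopping treatment or to missing the outcome interview, and on which patients enter the completer-only analysis.

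**Working it through.** **Inputs.** Standardised effect d = 0.53, alpha 0.05, power 0.80, dropout 20% and planned N = 70 (Sample Size); comparator 44 (Abstract); 42 recruited (Recruitment); 57% treatment dropout (Abstract, Introduction). Sidedness is not stated. Two-sided is used because it reproduces the plan's figure; one-sided gives 57 per arm after inflation, not 70.

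**Step 1: reproduce the plan's 70.**
n per arm = 2 × (1.960 + 0.842)² / 0.53² = 55.9, rounded up to 56.
Inflated for dropout: 56 / (1 − 0.20) = 70. This is an exact match, on a continuous effect size with equal arms.

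**Step 2: power at the real arm sizes.** Two-sample t test, noncentrality d × √(n1·n2/(n1 + n2)), n1 + n2 − 2 degrees of freedom.

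| Situation | Enrolled | Analysed | Noncentrality | Power |
|---|---|---|---|---|
| As the formula implies, 20% loss | 70 v 70 | 56 v 56 | 2.80 | 79% |
| Planned blended arm, real TAU arm, 20% loss | 70 v 44 | 56 v 35 | 2.46 | 68% |
| Recruited blended arm, real TAU arm, no loss | 42 v 44 | 42 v 44 | 2.46 | 68% |
| Recruited blended arm, real TAU arm, 20% loss | 42 v 44 | 34 v 35 | 2.20 | 58% |
| As above, 40% loss | 42 v 44 | 25 v 26 | 1.89 | 46% |

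Analysed numbers are enrolled × 0.80 (70 → 56; 44 → 35.2; 42 → 33.6) or × 0.60 (42 → 25.2; 44 → 26.4), rounded. The first row is 79% rather than 80% because the t distribution is slightly stricter than the normal formula of step 1, which gives 80.1% at 56 v 56.

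**Step 3: if the 44 are already the analysed patients.** The article does not say. Applying 20% loss to the blended arm only gives 56 v 44, power 74%, and 34 v 44, power 63%. Both remain below 80%.

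**Step 4: completer-only set, conditional.** If completer means treatment completer, and 57% stop treatment in both arms: 42 × 0.43 = 18.1 and 44 × 0.43 = 18.9, so about 18 v 19. Noncentrality 1.61, power 35%.

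**The case against.** **The 57% against the 20%.** A reader might infer that 57% dropout in the source RCT refutes the 20% allowance and makes both the power figure and the completer-only analysis untenable. The documents do not support that. Both places that give 57% tie it to treatment, whereas a sample-size allowance normally covers missing outcomes. The article reports no K-SADS loss for the RCT, and the intention-to-treat analysis on imputed data keeps patients who stop treatment. This objection stands, so the 57% is not used for the main result.

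**No arithmetic slip.** The 70 follows exactly from its inputs. This also stands. The fault is that those inputs assume a comparator of 70, not that they were combined wrongly.

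**The 18 v 19 figure.** Completer is not defined and may mean patients with observed outcomes; the 57% is not split by arm; and blended treatment is intended to reduce dropout. The figure is therefore a conditional illustration only. Leaving the definition of completer to a fuller document would be no fault in itself.

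**Too late to matter.** Enrolment has closed, and the confidence interval will show the precision achieved. That is true of the results, but the article reports 42 recruited and still presents 80% power for 70. Readers will use that figure when interpreting a null finding.

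**Imputation.** Imputing missing diagnoses keeps patients in the analysis. Information recovered from other measurements could lift power above 58%, but even complete data on 42 v 44 give only 68%.

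**Conclusion.** The design does not deliver the stated 80% power at its own effect size and its own 20% dropout. Power is about 68% with the planned blended arm against the real TAU arm, and about 58% with the patients actually recruited. The shortfall comes from arm sizes that the article itself reports, not from the 57%.

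The result assumes d = 0.53, a two-sided 5% test, equal loss in both arms, and 42 as the final blended count, since the article gives that number alongside the close of enrolment. It also uses a continuous effect size because that is what reproduces the 70. The primary outcome is a diagnosis, yes or no, and no rates are given, so power on that scale cannot be derived from the article without assumed rates.

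The dropout point is narrower. The Sample Size section does not say which kind of loss the 20% covers. If completer means treatment completer and 57% recurs, that set would have about 18 v 19 patients and 35% power, and would be selected on an event after baseline in a comparison that is already non-randomised.

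**What to change.** **Sample Size section.** Restate power for 42 v 44. Replace the assumed 20% with the loss of 12-month K-SADS interviews observed in the finished RCT, or show a range from 20% upward. If the 20% refers to missing outcome interviews, say so; that also removes the apparent clash with the 57%.

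**Analyses section.** State that the primary conclusion rests on the intention-to-treat analysis, and report the completer-only result as a sensitivity or descriptive analysis.

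**Cost.** Wording only. The stated power becomes less favourable, and no patients or assessments are added.
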